**Fig. 5 Fig5:**
[figure not shown]
An instruction sheet illustrates the procedure for clinician-collected oropharyngeal swabs

Six oropharyngeal swabs from the participants will be taken which consists of four standard-of-care specimens and two non-standard-of-care specimens. Table 3 shows the order and type of specimens collected at week 6 and 12 and the corresponding testing methods. Participants will be asked not to use mouthwash on the day of the clinic visit at week 6 and 12 to minimise the effect size if men only use mouthwash at the last minute.

**Table 3 Tab3:** Summary of oropharyngeal swabs collection at week 6 and week 12 follow up visits

Order of specimens	Type of specimen	Standard-of-care specimens	Testing method	Note
1	Tonsillar fossae	No	All sites: NAAT. The Aptima Combo 2 Assay (Hologic, Inc., CA, USA).	This will be tested in real time as part of stand-of-care specimen for participants recruited at the Melbourne Sexual Health Centre. Thus, swab number 2 is not required for participants recruited at the Melbourne Sexual Health Centre.
2	Tonsillar fossae	Yes	RPA Sexual Health: NAAT. Aptima Combo 2 assay on the Hologic Gen-Probe (San Diego, CA, USA)	Applies to all participating sites except the Melbourne Sexual Health Centre.
			Sydney Sexual Health Centre and Northside clinic: NAAT. Roche cobas 4800 CT/NG (Roche Diagnostic Systems, Branchburg, NJ, USA).	
			Western Sydney Sexual Health Centre: NAAT. BD ProbeTec™ ET System (Becton Dickinson, Sparks, MD, USA).	
3	Posterior oropharynx	No	All sites: NAAT. The Aptima Combo 2 Assay (Hologic, Inc., CA, USA).	This will be tested in real time as part of stand-of-care specimen for participants recruited at the Melbourne Sexual Health Centre. Thus, swab number 4 is not required for participants recruited at the Melbourne Sexual Health Centre.
4	Posterior oropharynx	Yes	RPA Sexual Health: NAAT. Aptima Combo 2 assay on the Hologic Gen-Probe (San Diego, CA, USA)	Applies to all participating sites except the Melbourne Sexual Health Centre.
			Sydney Sexual Health Centre and Northside clinic: NAAT. Roche cobas 4800 CT/NG (Roche Diagnostic Systems, Branchburg, NJ, USA).	
			Western Sydney Sexual Health Centre: NAAT. BD ProbeTec™ ET System (Becton Dickinson, Sparks, MD, USA).	
5	Tonsillar fossae	Yes	All sites: Culture. GC agar plate.	-
6	Posterior oropharynx	Yes	All sites: Culture. GC agar plate.	-

The non-standard-of-care oropharyngeal specimens (swabs number 1 and 3, Table 3) will be collected using cotton-tipped swabs and immediately placed into the Aptima specimen transfer tube containing the transport medium (Hologic, Inc., CA, USA). The Aptima transport medium will be pipetted into a sterile 2.0 mL micro tube and stored at −80 °C until testing. An aliquot of 200 μL of the Aptima transport medium will be placed on the MagNA Pure 96 Instrument (Roche Diagnostics, Mannheim, Germany) for DNA purification. The samples will be assessed for sampling and extraction adequacy by amplifying a 260 bp region of the human beta-globin gene [95]. The *N. gonorrhoeae* bacterial DNA load of the sample will be quantified using qPCR assays targeting the *N. gonorrhoeae opa* gene. All positive samples for the gonococcal *opa* gene will then be confirmed using a qPCR targeting the *N. gonorrhoeae porA* gene [96, 97]. All non-standard-of-care oropharyngeal specimens (swabs number 1 and 3, Table 3) will be batch tested at the Royal Women’s Hospital, Molecular Microbiology Laboratory, Melbourne.

The standard-of-care oropharyngeal specimens (swabs number 2, 4, 5 and 6, Table 3) will be undertaken locally as part of routine care at each participating clinic. Swabs number 2 and 4 will be tested by in-house NAAT methods. The Melbourne Sexual Health Centre, and RPA Sexual Health use the Aptima Combo 2 assay on the Hologic Gen-Probe (San Diego, CA, USA) PANTHER system. The Western Sydney Sexual Health Centre uses the strand displacement amplification (SDA) assay on the BD ProbeTec™ ET System (Becton Dickinson, Sparks, MD, USA). The Sydney Sexual Health Centre and the Northside Clinic use real-time polymerase chain reaction (PCR) on the Roche cobas 4800 CT/NG (Roche Diagnostic Systems, Branchburg, NJ, USA). These assays have been shown to have analytical sensitivity and specificity of 100% [99, 100]. Test results for oropharyngeal gonorrhoea at week 6 and week 12 will be given to the participants. Participants with a positive test will be recalled to the clinic for standard antibiotic treatment as per the Australian STI treatment guidelines [101]. Swabs 5 and 6 will be tested by in-house culture method. Results for standard-of-care oropharyngeal specimens will be recorded.

#### Full STI screening at week 12

All participants will have a STI screen at week 12 as per the Australian STI guidelines [102]. This includes oropharyngeal swabs for chlamydia by NAAT, first-void urine for urethral gonorrhoea and chlamydia by NAAT, anorectal swab for gonorrhoea and chlamydia by NAAT, and serology for HIV and syphilis. All specimens will be collected locally and will be tested by in-house methods at each participating clinic. Test results will be given to the participants. Participants with a positive test will be recalled to the clinic for standard antibiotic treatment as per the Australian STI treatment guidelines [101].

### Data collection

#### Questionnaire

Participants will be required to complete a self-administered questionnaire at baseline and at week 6 and week 12 at the clinic (Table 2). Participants will also be asked to complete a short questionnaire at week 3 and week 9 and return it by post. These questionnaires collect information on demographic characteristics (at baseline), history of mouthwash use (at baseline), antibiotic use, sexual risk behaviours, mouthwash adherence (after baseline), adverse events (after baseline) and mouthwash acceptability/tolerability (at week 12).

#### Mouthwash adherence monitoring

All five questionnaires will ask about mouthwash adherence. Participants will be required to report the number of days they use the OMEGA study mouthwash, how many times they use it per day, the volume they use each time, how they use it (i.e. rinse only; gargle only; both rinse and gargle) and the duration of the gargle/rinse each time. Participants will also be required to return the mouthwash bottles to the clinic at week 6 and 12. The volume left in the mouthwash bottle will be measured and recorded by the research nurse. High mouthwash adherence over a 2-week period has been reported among 10 MSM [103].

#### Antibiotic use

All five questionnaires will ask about use of antibiotics. If the participants report any antibiotic use, the name of the antibiotic and reason for use will also be asked. In signing the consent form, participants also consent to the research team contacting their general practitioner and other health professionals at their local clinic(s) to obtain the information on antibiotic use (i.e. date of prescription, name of antibiotics) and gonorrhoea diagnoses during the 12-week study period. A cover letter and data request form will be sent to the GP by the research nurse once the participants have completed the study.

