#### Inclusion criteria

Men who have sex with men and aged 16 years or above, and fulfil either (i) or (ii).(i)Men aged 16–24 years: tested positive or negative for oropharyngeal gonorrhoea by NAAT within the previous 30 days, as young MSM are at higher risk of oropharyngeal gonorrhoea [80].(ii)Men aged 25 years or above: tested positive for oropharyngeal gonorrhoea by NAAT within the previous 30 days, as this population has a higher rate of repeat diagnosis of gonorrhoea within 90 days [88].
Provide written informed consent.Provide consent for the research team to contact their health professional and/or GP to clarify the use and name of any antibiotics used during the study period.Have sufficient English language proficiency to understand the study requirements.Men co-infected with HIV or other STIs are eligible.

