### Loss to follow-up

Participants will be considered ‘lost to follow up’ if they do not attend for the week 12 clinic visit by 14 weeks since the baseline visit.

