#### Primary analysis

The primary end-point will be the proportion of men who have gonorrhoea detected in the oropharynx by NAAT at any time within 12 weeks in any specimen (saliva and/or oropharyngeal swabs). The proportion of men with oropharyngeal gonorrhoea detected will be compared between both groups. The 95% confidence intervals (CI) of the proportion of men with oropharyngeal gonorrhoea will be calculated based on the ‘exact’ binomial confidence intervals [106]. The two study arms will be compared using logistic regression. Multivariate logistic regression will be performed to adjust any imbalance of baseline characteristics and potential confounding factors. Men with symptomatic urethral gonorrhoea may attend clinical services between the two clinic visits and test positive for oropharyngeal gonorrhoea. Any positive oropharyngeal results will be included in the analysis unless they were taken within 3 weeks of treatment because within 3 weeks NAAT results may represent residual non-viable DNA from the previous infection [107].

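### The outside-record request is tied to completing the study, and no lookup is stated for men lost to follow-up, so late endpoint ascertainment can depend on retention

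*Protocol article*

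**What the plan says.** Five sections of the protocol article bear on this.

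- **Antibiotic use.** By signing the consent form, every participant lets the team ask his GP and other local clinicians for antibiotic details, including prescription dates, and for "gonorrhoea diagnoses during the 12-week study period". The timing of the request is: "A cover letter and data request form will be sent to the GP by the research nurse once the participants have completed the study".
- **Inclusion criteria.** Entry requires a man to "Provide consent for the research team to contact their health professional and/or GP to clarify the use and name of any antibiotics used". This item names antibiotics only; the Antibiotic use section extends the consent to diagnoses.
- **Loss to follow-up.** A man is lost "if they do not attend for the week 12 clinic visit by 14 weeks since the baseline visit". The section says nothing about requesting records for such men.
- **Statistical methods.** The primary analysis is by intention to treat among men with at least one follow-up swab.
- **Primary analysis.** The endpoint is gonorrhoea by NAAT in saliva or swab at any time within 12 weeks. The section notes that men may attend services between visits, and then states: "Any positive oropharyngeal results will be included in the analysis unless they were taken within 3 weeks of treatment".

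**The concern.** Positives found between visits count towards the primary endpoint. For results from other providers, the record request is the only stated way of obtaining them. If that request goes out only for men who attended week 12, completers get scheduled tests plus a record search, while a man who left after week 6 gets neither from then on. He nevertheless stays in the denominator on the strength of his week 6 swab.

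The 3-week exclusion is affected too. The questionnaires ask for the antibiotic's name and the reason for use; the date of prescription appears only in the record request. Suppose a man is treated elsewhere, posts a positive week 9 saliva and then misses week 12. Without the request there is no stated source for the outside prescription date needed to judge that specimen.

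At stake is whether the endpoint is measured in the same way for men who stay and men who leave. If leaving is related to arm, that difference passes into the treatment comparison.

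**Working it through.** **1. The plan's own figures.** The Sample size section gives 438 evaluable men for 20% versus 10% at 80% power. The two-proportion formula with continuity correction, two-sided 5%, gives 219 per arm, or 438. The recruited total is 438 × 1.15 = 504 (503.7 rounded up), or 252 per arm. Both reproduce.

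**2. Men lost.** 504 × 0.15 = 75.6, about 76, or 38 per arm if loss is equal.

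**3. Risk in the unobserved period.** Assume a constant hazard over 12 weeks and departure straight after week 6.
- Control: 1 − √(1 − 0.20) = 0.106.
- Intervention: 1 − √(1 − 0.10) = 0.051.

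**4. Infections in that period, both arms together.**
- At the planned rates: 38 × 0.106 + 38 × 0.051 = 4.0 + 1.9, about 6.
- With all 76 at the control rate: 76 × 0.106, about 8.

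**5. Expected events, both arms together.**
- 219 per arm: 219 × 0.20 + 219 × 0.10 = 65.7, about 66.
- 252 per arm: 252 × 0.20 + 252 × 0.10 = 75.6, about 76.

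**6. Effect on the risk ratio (true value 0.50).** The document gives no loss by arm and no risk among men lost, so the inputs below are assumptions.

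(a) *Men lost stay in the denominator and nothing is captured after week 6.* Their hazard equals that of the others in their arm. Observed risk = (1 − d) × 12-week risk + d × 6-week risk, where d is the arm's loss.

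| Loss, control / intervention | Control | Intervention | Ratio |
|---|---|---|---|
| 15% / 15% | 0.186 | 0.093 | 0.499 |
| 10% / 20% | 0.191 | 0.090 | 0.474 |
| 20% / 10% | 0.181 | 0.095 | 0.525 |

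(b) *Nothing at all is captured from men lost, so only completers are seen.* Observed risk = p / (1 − d + d × r), where p is the arm's true risk and r is the risk of men lost relative to completers.

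| Loss, control / intervention | r, control / intervention | Control | Intervention | Ratio |
|---|---|---|---|---|
| 15% / 15% | 0.5 / 0.5 | 0.216 | 0.108 | 0.50 |
| 15% / 15% | 1 / 1 | 0.200 | 0.100 | 0.50 |
| 15% / 15% | 2 / 2 | 0.174 | 0.087 | 0.50 |
| 15% / 15% | 1 / 2 | 0.200 | 0.087 | 0.435 |
| 15% / 15% | 2 / 1 | 0.174 | 0.100 | 0.575 |
| 10% / 20% | 2 / 2 | 0.182 | 0.083 | 0.458 |
| 20% / 10% | 2 / 2 | 0.167 | 0.091 | 0.545 |

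With equal loss and equal relative risk the ratio is essentially unchanged. It moves only when one of these differs by arm. Set (b) is a worst case, because earlier specimens from men lost would shrink the shifts.

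**The case against.** The strongest reply is that the sentence is about timing. The records cover the 12-week period, so a request has to follow its end, and completing the study may simply mean that a man's 12 weeks are over. The text does not say that only attenders are looked up, consent does not depend on attendance, and a condensed article may leave the handling of letters to the full protocol. This stands as far as it goes: a reader might infer that men who leave are never looked up, and the document does not say so. It does, however, state a trigger, and no section supplies another. Two readings that give different endpoint ascertainment for up to 15% of men are reason enough to reword it.

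A reader might also infer that records are the only endpoint source for men who leave. They are not. Loss means a missed week 12 visit, and specimens from weeks 3, 6 and 9 count; the week 9 pack is handed out at week 6 and posted back. Records are the only stated source only for the time after the last specimen. Returned questionnaires also give some antibiotic information, and the Treatment section says antibiotics given will be recorded, but neither is stated to supply outside prescription dates.

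A third tempting reading is that attrition bias is built in. The rule is the same in both blinded arms, and differential loss is not shown. The Blinding section concedes that taste is not identical, but also reports that none of the clinic staff who tried the two solutions could tell them apart.

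Finally, the infection count is an upper bound. The Background says extra-genital infections are mainly asymptomatic, so many would never have an outside diagnosis to find. That stands, and it limits the size of the point.

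**Conclusion.** The point holds as a risk arising from how one sentence is fixed. Followed literally, ascertainment after a man's last specimen depends on whether he completes, although his consent covers the lookup and the Primary analysis section would count the result. Bias in the treatment effect is possible if loss, or risk among men lost, differs by arm; nothing in the document shows that it exists.

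The size is modest: at most about 6 to 8 infections over both arms, against about 66 to 76 expected. This rests on the planned 20% and 10% rates (the 8 applies the control rate to everyone lost), the full 15% loss, a constant hazard, every lost man leaving just after week 6, and no week 9 saliva from any of them. The share that records would recover is not given. Confidence is moderate because the phrase can be read in two ways. The change is still worth making, since it removes the dependence on attendance at almost no cost.

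**What to change.** In the Antibiotic use section, replace the completion trigger with a fixed time: send the request for every randomised man at 14 weeks after baseline, whether or not he attended week 12, unless he withdrew that consent. The period asked about stays the 12-week study period. Fourteen weeks is already the cut-off in the Loss to follow-up section.

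In the Primary analysis section, state that record-based positives are judged by the same 3-week rule for every man in the primary set, that is, with at least one follow-up swab. Use record positives from men with no follow-up swab only in a sensitivity analysis. Counting them in the primary analysis would add events from men whose untested counterparts cannot enter as negatives.

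The cost is a few sentences and about 76 more letters. Some GPs will not reply, and men who left will still lack scheduled tests, so the change narrows the gap in ascertainment without closing it.

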### Treatment

Participants with any STI during the study period will be treated as per the Australian STI guidelines [83]. Any antibiotic given to the participants will be recorded.

### Adverse events

Adverse event and tolerability data will be measured from the questionnaires every 3 weeks. The Medical Dictionary for Regulatory Activities (MedDRA) will be used for reporting any adverse events. No adverse events were reported from a previous longitudinal study involving 10 men who used mouthwash every day for 14 days [103].

### Loss to follow-up

Participants will be considered ‘lost to follow up’ if they do not attend for the week 12 clinic visit by 14 weeks since the baseline visit.

### Compensation

Reimbursement is necessary to compensate participants for their participation in the trial and to maximize retention. Participants will receive an AU$100 gift voucher when they attend the clinic in person at week 12. Similar reimbursements have been used in a cohort study among MSM with four clinic visits with 85% retention at 12 months [104].

### Statistical methods

Data will be analysed in Stata (version 13 Stata Corp., College Station, TX, USA). The primary analysis will be an intention to treat analysis for all those with at least one follow up swab. The demographic characteristics and sexual risk behaviours will be compared between the control and intervention arm to ensure the balance in the baseline characteristics in both arms [105].

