#### Follow up

Participants will be followed up every 3 weeks during the 12-week trial which consists of two face-to-face clinic visits (at week 6 and 12) and two home-based specimen and data collection postal packs (at week 3 and 9).

The week 6 and week 12 follow up visits will be a face-to-face visit and will be conducted at the participating clinics. The follow up time points at week 3 and week 9 will consist of a questionnaire and home-based saliva collection, to be posted back to the Melbourne Sexual Health Centre. The home-based study pack will be disseminated to the participants at both baseline and week 6 clinic visits for week 3 and week 9 home-based study pack, respectively. The home-based study pack consists of: a questionnaire, a yellow cap specimen collection jar, an UriSwab (Copan Diagnostics, Brescia, Italy) for saliva collection, an instruction sheet for saliva collection (Fig. 4) and a prepaid padded postage bag addressed to the Melbourne Sexual Health Centre. All home-based study packs will be returned to the Melbourne Sexual Health Centre only for specimen processing, leaving all clinics to focus on recruitment and clinic visits.

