#### Saliva

Participants will be required to self-collect a saliva sample every 3 weeks. Figure 4 illustrates how to self-collect a saliva sample. This instruction sheet will be given to the participants and a video clip is available on the OMEGA study website for participants to review the procedure (www.mshc.org.au/omega). In brief, participants will be instructed to accumulate saliva in the mouth for about 30 seconds to get a reasonable volume of saliva. Participants will spit as much saliva as possible into a yellow cap specimen collection jar, and saliva will be collected by using an UriSwab (Copan Diagnostics, Brescia, Italy). Saliva samples at week 6 and week 12 will be collected at the participating clinic under the research nurse’s supervision; while saliva samples at week 3 and week 9 will be collected at home by participants. All saliva specimens collected will be transported by using UriSwab.

All participants will be required to send their home-based collected UriSwabs to the Melbourne Sexual Health Centre at week 3 and 9 by post. The research nurse at each participating clinic will be required to send clinic-based collected UriSwabs to the Melbourne Sexual Health Centre at week 6 and 12 by post.

Once the research team at the Melbourne Sexual Health Centre receives the UriSwab by post, the UriSwab will be immediately centrifuged at 1200 g for 1 min to separate the saliva from the UriSwab sponge. The centrifuged saliva will be pipetted into a sterile 2.0 mL micro tube (Scientific Specialties, Inc., CA, USA) and stored at −80 °C freezer at the Melbourne Sexual Health Centre for testing.

All centrifuged saliva samples will be batch tested at the Royal Women’s Hospital, Molecular Microbiology Laboratory, Melbourne. The saliva samples will be placed on the MagNA Pure 96 Instrument (Roche Diagnostics, Mannheim, Germany) for DNA purification and will be assessed for sampling and extraction adequacy by amplifying a 260 bp region of the human beta-globin gene [95]. The gonococcal bacterial DNA load of the sample will be quantified using qPCR assays targeting the *N. gonorrhoeae opa* gene. All samples positive for the *opa* gene will then be confirmed using a qPCR targeting the *N. gonorrhoeae porA* gene [96, 97].

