#### Oropharyngeal swabs

Pharyngeal specimens will be collected at week 6 and week 12 clinic visits. All oropharyngeal swabs will be collected by the research nurses at each participating site. All swabs will be taken by no more than two research nurses at each site to minimise the variability of sampling technique [98]. All research nurses at each site will be trained on how to take a oropharyngeal specimen for this study, and an instruction sheet and a video clip will be provided to the research nurses to review the procedure (Fig. 5).

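### The primary analysis set requires a follow-up swab, but the primary endpoint can be met on saliva alone, so men with endpoint data can fall outside the set

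*Protocol article*

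**What the plan says.** Four statements in the protocol article bear on this point.

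- **Analysis set** (Statistical methods): "The primary analysis will be an intention to treat analysis for all those with at least one follow up swab".
- **Endpoint** (Primary analysis): NAAT detection in the oropharynx "at any time within 12 weeks in any specimen (saliva and/or oropharyngeal swabs").
- **Schedule.** Swabs: "Pharyngeal specimens will be collected at week 6 and week 12 clinic visits". Saliva: "Participants will be required to self-collect a saliva sample every 3 weeks", and in Follow up, "The follow up time points at week 3 and week 9 will consist of a questionnaire and home-based saliva collection". Table 2 agrees: weeks 3 and 9 have saliva and no swab.
- **Comparison** (Primary analysis): "The two study arms will be compared using logistic regression". The outcome is detected or not detected, with adjustment for baseline imbalance and potential confounders.

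Loss to follow-up is defined by the last visit only: "Participants will be considered ‘lost to follow up’ if they do not attend for the week 12 clinic visit by 14 weeks since the baseline". A man can therefore be lost and still have a week-6 swab, or have only saliva. The Secondary analysis section adds a survival analysis that allows repeat events, and a repeated-measures logistic regression at weeks 6 and 12.

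**The concern.** The endpoint and the set are both fixed in the article, and they do not match. A man who posts a positive week-3 saliva specimen and never returns to the clinic has met the endpoint but is not in the denominator. A man with only negative saliva results is lost in the same way. Membership turns on returning to the clinic after randomisation. The Blinding section concedes that the tastes are not identical and that blinding by taste cannot be guaranteed, and tolerability is itself an outcome. Attendance could therefore differ by arm, although nothing in the article shows that it will.

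A secondary issue concerns men who are in the set but incompletely observed. The primary model takes no account of how long a man was followed. A man with a negative week-6 swab who then leaves would enter as not detected, alongside a man negative at all four time points, unless missing results are handled in some way the article does not describe. If such loss differed by arm, the arm with more of it would look better.

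**Working it through.** **1. The plan's own figure.** Inputs from Sample size: 20% versus 10%, 5% significance (taken as two-sided), 80% power.

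- Uncorrected n per arm = [1.96·√(2·0.15·0.85) + 0.8416·√(0.2·0.8 + 0.1·0.9)]² / 0.10² = (0.990 + 0.421)² / 0.01 ≈ 199.
- With continuity correction, n = (199/4)·[1 + √(1 + 4/(199·0.10))]² ≈ 219 per arm, or 438 in total. This matches the article.

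**2. Who has endpoint data, and who is in the set**

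| Follow-up specimens | Endpoint data? | In the primary set (plain reading)? |
|---|---|---|
| Week-3 saliva only, positive | Yes, endpoint met | No |
| Week-3 saliva only, negative | Yes, partial | No |
| Week-6 swab negative, then leaves | Yes, partial | Yes |
| Any swab positive | Yes, endpoint met | Yes |
| None | No | No |

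**3. Positives that could be dropped.** Recruitment is 504 (252 per arm) with up to 15% loss: 0.15 × 252 = 37.8 per arm, about 76 in all. The article does not say when men leave, so the extreme case is taken, in which all leave before week 6. Further assumptions: constant hazard over 12 weeks, and 25–50% of these men having returned week-3 saliva.

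- Men with saliva only: 0.25 × 75.6 ≈ 19, up to 0.50 × 75.6 ≈ 38.
- Three-week risk = 1 − (1 − p)^(3/12): 5.4% if p = 20%, 2.6% if p = 10%.
- At the design rates, with every such man returning saliva: 37.8 × 0.0543 ≈ 2.1 control and 37.8 × 0.0260 ≈ 1.0 intervention positives, 3.0 in all. At 25–50% return: 0.8–1.5.
- With 20% risk in both arms: 19 × 0.0543 ≈ 1.0, up to 37.8 × 0.0543 ≈ 2.1.

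So about 1–2 positives are at stake in the whole trial.

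**4. Equal loss after week 6.** Assume 15% of each arm leaves after the week-6 swab and nothing later is seen. Six-week risk is 1 − √0.8 = 10.6% and 1 − √0.9 = 5.1%.

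- Control: 0.85 × 0.20 + 0.15 × 0.106 = 18.6%.
- Intervention: 0.85 × 0.10 + 0.15 × 0.051 = 9.3%.
- The difference is 9.3 points instead of 10. The risk ratio is still about 0.50.

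**5. Unequal loss after week 6, no true effect** (20% in both arms)

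| Loss, control vs intervention (assumed) | Detected, control vs intervention | Risk ratio |
|---|---|---|
| 5% vs 15% | 19.5% vs 18.6% | 0.95 |
| 0% vs 15% | 20.0% vs 18.6% | 0.93 |
| 10% vs 30% | 19.1% vs 17.2% | 0.90 |

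In the first row the spurious gap is about 0.9 points. The standard error at 252 per arm is √(2 × 0.19 × 0.81 / 252) ≈ 3.5 points, so the gap is about 0.27 standard errors, and a nominal 5% test would reject about 5.8% of the time. The last row averages 20% loss, above the planned maximum of 15%.

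**The case against.** **The word swab may cover saliva.** The Saliva section says "saliva will be collected by using an UriSwab (Copan Diagnostics, Brescia, Italy"), and the analysis-set sentence does not specify oropharyngeal swabs. On that reading no saliva result is dropped. This is possible but strained, because the endpoint sentence lists saliva and oropharyngeal swabs as separate specimens. The Primary analysis section also says that positive oropharyngeal results count unless taken within 3 weeks of treatment, which pulls against discarding one. These points argue for settling the text. They do not remove the mismatch.

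**Early leavers as 12-week negatives.** A reader might infer that the plan scores everyone who leaves early as negative. The article does not say so. Men who leave before any swab are excluded, not scored negative, and men already positive count as positive. Only men with a negative swab who leave before week 12 could be affected, and missing-data handling may sit in an analysis plan that is not shown. This part of the objection stands, and it is why the time-observed issue is secondary here.

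**Unequal follow-up is partly handled.** The Primary outcome section names cumulative incidence, the Secondary analysis section plans a survival comparison, and diagnoses are sought from other clinicians, so time after a missed visit is not wholly unseen. This stands in part. The survival comparison is listed as secondary, and its minimum of two follow-up periods does not fit a man whose only follow-up test is at week 6. The repeated-measures analysis uses weeks 6 and 12 only, so it leaves out the home saliva.

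**The label is a formality.** The restriction is stated openly, and a set based on any valid specimen also depends on participation after randomisation. That is so, which is why the replacement should not be called intention to treat either. It does, however, keep every man with endpoint data.

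**Conclusion.** The mismatch holds on the plain reading. The primary set is defined by a swab, the endpoint by any specimen, and men with saliva results only are left out of an analysis labelled intention to treat. This conflict lies between two stated rules and is not missing detail.

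The size is modest. About 1–2 positives would be dropped even if all of the planned loss fell before week 6 and 25–50% of those men had sent week-3 saliva. Equal late loss costs about 0.7 points of the 10-point difference and leaves the risk ratio near 0.50.

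A reader might go further and conclude that the primary result will be biased in favour of the antibacterial mouthwash. The documents do not support that. A spurious risk ratio of about 0.95 needs an assumed differential loss such as 15% versus 5%, and the article gives no reason to expect that split. The 19–38 saliva-only men are likewise an upper range, since they require all lost men to leave before week 6.

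The calculations assume a constant hazard, the chosen timing of loss and the chosen saliva return. The point should be corrected before analysis, but it ranks below a must-fix.

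**What to change.** 1. Define the primary set as all randomised men with at least one valid follow-up NAAT result, saliva or swab, analysed in the arm assigned. Say what makes a result valid, drawing on the specimen-adequacy check and the 3-week post-treatment exclusion already in the article.
2. Describe the set in those words and drop the intention-to-treat label.
3. Add a sensitivity analysis of all randomised men, stating how men with no follow-up result are handled.
4. State how men without week-12 data enter the primary comparison. Support that comparison with an analysis that credits only observed time and uses the home saliva: a discrete-time (complementary log-log) model over the 3-week intervals, or multiple imputation of missing results by arm.

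The cost is a wording change and a modest amount of extra analysis. No new data, visits or participants are needed. The wording should be settled before unblinding.
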